There are two factors to be considered for the OXY111A dose escalation part of this study: total dose administered and infusion rate. The human equivalent dose-corrected No Observed Adverse Effect Level (NOAEL) in rats was 15’000 mg/m^2^ once a week for 5 weeks, while it was 43’750 mg/m^2^ in minipigs also once weekly (unpublished data obtained from Normoxys®). From animal studies, hypernatremia is known to be associated with high plasma concentrations typically encountered at the end of the OXY111A infusion and probably associated with infusion rate. Therefore, infusion rates of not more than 750 mg/m^2^/min are recommended. According to available phase I data in healthy volunteers (unpublished data obtained from Normoxys®), cohort 1 starts at a dose close to 5’600 mg/m^2^ weekly, i.e. 1866 mg/m^2^ thrice weekly. Dose escalation is performed according to the following scheme up to a maximum calculated dose of 43’700 mg/m^2^ weekly, which corresponds to the NOAEL level administered once weekly in minipigs.

Table 1 schedules dose escalation. In each cohort, 3 patients will be included (Table 1).

**Table 1 Tab1:** Dose escalation scheme

Cohort No.	Weekly Dose	Single Dose	Total Dose (9 applications )	% Dose Escalation
1	5'598 mg/m^2^	1'866 mg/m^2^	16'794 mg/m^2^	baseline
2	11'196 mg/m^2^	3’732 mg/m^2^	33'588 mg/m^2^	100 %
3	16'800 mg/m^2^	5‘600 mg/m^2^	50‘400 mg/m^2^	50 %
4	21‘000 mg/m^2^	7‘000 mg/m^2^	63‘000 mg/m^2^	25 %
5	26‘250 mg/m^2^	8‘750 mg/m^2^	78‘750 mg/m^2^	25 %
6	31‘500 mg/m^2^	10‘500 mg/m^2^	94‘500 mg/m^2^	20 %
7	37‘170 mg/m^2^	12'390 mg/m^2^	111‘510 mg/m^2^	18 %
8	43'500 mg/m^2^	14'500 mg/m^2^	130'500 mg/m^2^	~17 %

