The infusion rate must not be above 750 mg/m^2^/min. In order to achieve this, a constant infusion rate at 1/10 of the NOAEL infusion rate is chosen: an infusion rate of 75 mg/m^2^/min is scheduled for all dose steps. Due to the short half-life of OXY111A and the proposed mechanism of action, a slow, constant infusion over several hours appears more promising than a short infusion leading to excessively high concentrations of the compound.

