### Assessment of primary outcome

The primary outcome, safety and tolerability (establishing MTD) of the investigational medical product (IMP) will be assessed at every application for each patient. According to the 3 + 3 dose escalation schedule, after each patient, a decision on the continuation will be taken, i.e. to either add an additional patient in the same cohort or to continue with the next cohort after three patients.

Assessment will be done using CTCAE. The obtained data will be added to the electronic case report form (eCRF) using the software secuTrial® (interActive Systems GmbH (iAS), Berlin/Germany).

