### Pharmacokinetics

Blood samples are taken before OXY111application as well as at 3 and 6 hours after application start and 30 minutes, 1, 2 and 40 hours following application. Plasma levels of OXY111A are measured by Swiss BioAnalytics AG (Birsfelden, Switzerland) under ICH Good Laboratory Practice (GLP) conditions and validated by Food and Drug Administration (FDA) and European Medicines Agency (EMA) guidance [12].

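### At 75 mg/m²/min the planned doses infuse in 25 to 193 minutes, not the several hours used to justify that rate, and no pharmacokinetic draw is tied to the end of infusion

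*Protocol article*

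**What the plan says.** All statements are in the protocol article.

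- **Rate** (Dose escalation and extension): "The infusion rate must not be above 750 mg/m^2^/min". One tenth of this is chosen, so "an infusion rate of 75 mg/m^2^/min is scheduled for all dose steps".
- **Reason** (same section): the article concludes that "a slow, constant infusion over several hours appears more promising than a short infusion", and points to the compound's rapid elimination and how it is thought to work. The alternative it rejects is "a short infusion leading to excessively high concentrations of the compound".
- **Doses** (Table 1): single doses rise from 1,866 mg/m² in cohort 1 to 14,500 mg/m² in cohort 8, three times weekly. A DLT in cohort 1 lowers the weekly dose to 4,200 mg/m².
- **Why the end of infusion matters** (same section): "From animal studies, hypernatremia is known to be associated with high plasma concentrations typically encountered at the end of the OXY111A infusion".
- **Draws** (Pharmacokinetics): one before the application, then "at 3 and 6 hours after application start and 30 minutes, 1, 2 and 40 hours following application".

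**The concern.** The rate, the doses and the reason for the rate are all stated, and they do not fit together. A fixed rate makes duration proportional to dose. The lowest cohort, where every trial begins, gets the shortest infusion, which is the kind the rationale argues against. A reader cannot tell whether the rate or the intended duration is the error.

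The sampling times look as if they were set for longer infusions. The article names the concentration at the end of infusion as the one associated with hypernatremia in animals, and wants to avoid very high concentrations. Yet no draw is timed to that moment. What is at stake is a directly measured peak that could be set against the safety findings, and a rationale that matches what patients receive.

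**Working it through.** **1. The plan's own figure.** 750 / 10 = 75 mg/m²/min, so the stated rate reproduces.

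**2. Durations and draw times.** Duration T (min) = Table 1 single dose / 75. The offset of a draw from the end of infusion is 180 − T or 360 − T; a plus sign means after the end.

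| Cohort | Single dose (mg/m²) | T (min) | 3 h draw (min) | 6 h draw (min) |
|---|---|---|---|---|
| 1 | 1,866 | 24.9 | +155.1 | +335.1 |
| 2 | 3,732 | 49.8 | +130.2 | +310.2 |
| 3 | 5,600 | 74.7 | +105.3 | +285.3 |
| 4 | 7,000 | 93.3 | +86.7 | +266.7 |
| 5 | 8,750 | 116.7 | +63.3 | +243.3 |
| 6 | 10,500 | 140.0 | +40.0 | +220.0 |
| 7 | 12,390 | 165.2 | +14.8 | +194.8 |
| 8 | 14,500 | 193.3 | −13.3 | +166.7 |

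Assuming the de-escalation dose is also given three times weekly, it is 4,200 / 3 = 1,400 mg/m², and 1,400 / 75 = 18.7 min.

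Two cohorts finish within 1 h and five within 2 h; only cohort 8 exceeds 3 h. To be running still at 3 h, an infusion needs a dose above 75 × 180 = 13,500 mg/m². At 6 h it needs 75 × 360 = 27,000 mg/m², about 1.9 times the top dose.

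**3. How far the nearest draws are from the peak.** I read the draws following application as timed from the end of infusion, since the text separates them from those timed from the start. The first draw after the end is then at 30 min in cohorts 1 to 6 and at 14.8 min in cohort 7. The article gives no half-life, so I assume one-compartment decline with half-life h of 15, 30, 60 or 120 min. The fraction left is 0.5^(t/h):

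- t = 30 min: 25%, 50%, 71%, 84%
- t = 14.8 min: 50%, 71%, 84%, 92%
- cohort 8, 13.3 min before the end: within 4% of the end level

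**4. What a draw at the end would add.** For a log-linear fit, the standard error of the back-extrapolated log end level, relative to one direct sample, is sqrt(1/n + mean(t)²/Sxx). The 40 h draw is left out.

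- Five later draws quantifiable, cohort 1, present times 30, 60, 120, 155.1, 335.1: 0.737. With the 3 h draw moved to the end (0, 30, 60, 120, 335.1): 0.605. Over cohorts 1 to 7 the ranges are 0.72 to 0.76 now and 0.60 to 0.69 after.
- Only the 30 and 60 min draws quantifiable: sqrt(1/2 + 45²/450) = 2.24 now, and sqrt(1/3 + 30²/1800) = 0.91 with a draw at the end.

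**5. How tight the window must be.** The level k min before the stop, as a fraction of the end level, is (1 − 0.5^((T−k)/h)) / (1 − 0.5^(T/h)). Over the four half-lives:

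- k = 2: 92% to 96% in cohort 1, at least 96% in cohorts 2 to 8, and about 90% to 93% at the de-escalation dose
- k = 5: only 81% to 88% in cohort 1

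**The case against.** The strongest reply is that the operative instruction is the rate, which is unambiguous; the multi-hour phrase is background reasoning, and nobody would dose a patient differently because of it. Cohorts 6 to 8, at 2.3 to 3.2 h, fit it loosely. This limits the weight of the point but does not remove the contradiction for cohorts 1 to 5. Dividing the weekly dose by the rate does not rescue the phrase: the dose is given in three applications, and cohort 1 would still run only 5,598 / 75 = 75 min.

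Second, a condensed article may leave exact sampling times to the full protocol. That would answer a complaint about missing detail. Here the draw times are stated, and they do not match the stated doses and rate.

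Third, the hypernatremia risk is handled in other ways. The rate is one tenth of the limit in every cohort, and under linear kinetics a constant rate caps the peak whatever the dose. Safety "will be assessed at every application for each patient". All of this stands.

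Four stronger readings are tempting, and the document does not support them:

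- **That the 3 and 6 h draws were meant as end-of-infusion samples and miss their target.** The article never calls them that. It supports only that no draw is tied to the end.
- **That escalation or the MTD is compromised.** No DLT, TET or MTD rule uses a plasma level.
- **That a measured peak brings a large gain in precision.** That needs the later draws to be unquantifiable. It is plausible only at an assumed 15 min half-life in cohorts 1 to 3, where the 2 h and 3 h draws would hold under 1% of the end level. No assay limit is given to show that this is unmeasurable.
- **That inserting the real durations into the present sentence settles the matter.** The sentence would then prefer a 25 min infusion to a short one. The argument itself has to change.

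**Conclusion.** The point holds in a limited form and should be corrected. The contradiction between rate and rationale is arithmetic and needs no assumption for the eight Table 1 doses: clear in cohorts 1 to 5, arguable in cohorts 6 to 8. The de-escalation figure assumes three applications a week.

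The sampling mismatch is equally firm for the draws timed from the start. That no draw is tied to the end of infusion depends on reading the remaining draws as timed from its end. The consequence is modest: the later draws still describe the decline, and the peak can be back-extrapolated if that decline is log-linear. Every figure for the size of the loss depends on the assumed half-lives of 15 to 120 min and on which draws are quantifiable. Dose escalation decisions do not change.

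**What to change.** **1. Make rate and rationale agree** (Dose escalation and extension). If 75 mg/m²/min is intended, state the actual durations, about 19 to 193 min including the de-escalation dose. Drop the claim that the infusion lasts several hours, and rest the choice on the rate being one tenth of the limit. If several hours is intended, correct the rate instead. No single constant rate can give similar durations, because doses span 14,500 / 1,866 = 7.8-fold. A 3 h infusion in every cohort would need 1,866 / 180 = 10.4 rising to 14,500 / 180 = 80.6 mg/m²/min, so rate would increase along with dose.

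**2. If 75 mg/m²/min stands, move one draw** (Pharmacokinetics). Replace the draw at 3 h from the start with one in the last 2 min of infusion, and keep all others. Under the assumed half-lives it captures about 90% or more of the end level at every dose.

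**Cost.** One rewritten sentence and one changed sampling time; the number of draws is unchanged. The 2 min window has to be timed separately for each dose level, and the common 3 h time point is lost. In cohorts 2, 3, 5 and 6 the 3 h draw lies only 10.2, 14.7, 3.3 and 10.0 min from another scheduled draw, so little is given up there. In cohorts 1 and 4 the nearest other draw is 35.1 and 26.7 min away, so slightly more is lost. In cohorts 7 and 8 the moved draw replaces one already within 15 min of the end.

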### Study population and number of patients

Patients with primary and secondary hepato-pancreato-biliary and gastrointestinal neoplasia will be assessed for eligibility at the interdisciplinary tumor board of the Swiss HPB Center. Patient information and informed consent will be obtained in the outpatient and inpatient hospital setting. Overall, a maximum of 69 patients will be included consisting of maximum of 48 in the dose escalation and 21 patients in the extension part of the study. OXY111A will be administered in an outpatient setting in the Phase I unit of the Clinical Trials Center of the University Hospital Zurich, in which the study equipment is reserved for this study explicitly. Appropriate back up material will be available in case of technical dysfunction. The study is planned to be completed within approximately two years.

### Inclusion criteria

Participants fulfilling all of the following inclusion criteria are eligible for the study:Informed Consent as documented by signaturePatients diagnosed for non-resectable hepato-pancreato-biliary or gastrointestinal neoplasmMale and Female patients ≥ 18 years of ageEastern Cooperative Oncology Group (ECOG) performance status score of ≤ 2 at study entry.A life-expectancy of >3 monthsAdequate hematologic function, as defined by○ an absolute neutrophil count of >1000/mm^3^
○ a hemoglobin level of >10 g/dL○ a platelet count of >100,000/mm^3^

Adequate renal function, as defined by a serum creatinine level of ≤1.5 x the upper normal limit.Use of effective contraception. Female patients who are surgically sterilized/hysterectomized or post-menopausal for longer than 2 years are not considered as being of procreative potential.Adequate recovery from recent surgery, chemotherapy and radiation therapy. At least 28 days must have been elapsed from major surgery, prior chemotherapy, prior treatment with an investigational agent or device, or prior radiation therapy (palliative radiation therapy is allowed).Accessible for treatment and follow-up. Patients enrolled in this trial must be treated at the participating center.

### Exclusion criteria

The presence of any of the following exclusion criteria will lead to exclusion of the potentially eligible participant:Contraindications to the class of drugs used in this study, e.g. known hypersensitivity or allergy to class of drugs or the investigational productWomen who are pregnant or breast feedingIntention to become pregnant during the course of the studyLack of safe contraception, defined as: Female participants of childbearing potential, not using and not willing to continue using a medically reliable method of contraception for the entire study duration, such as oral, injectable, or implantable contraceptives, or intrauterine contraceptive devices, or who are not using any other method considered sufficiently reliable by the investigator in individual cases. Please note that female participants who are surgically sterilised / hysterectomised or post-menopausal for longer than 2 years are not considered as being of child bearing potential.Other clinically significant concomitant disease states (e.g., renal failure, hepatic dysfunction, cardiovascular disease, etc.)Known or suspected non-compliance, drug or alcohol abuseInability to follow the procedures of the study, e.g. due to language problems, psychological disorders, dementia, etc.Participation in another study with investigational drug within the 30 days preceding and during the present studyPrevious enrolment into the current studyEnrolment of the investigator, his/her family members, employees and other dependent persons.

### Assessment of primary outcome

The primary outcome, safety and tolerability (establishing MTD) of the investigational medical product (IMP) will be assessed at every application for each patient. According to the 3 + 3 dose escalation schedule, after each patient, a decision on the continuation will be taken, i.e. to either add an additional patient in the same cohort or to continue with the next cohort after three patients.

Assessment will be done using CTCAE. The obtained data will be added to the electronic case report form (eCRF) using the software secuTrial® (interActive Systems GmbH (iAS), Berlin/Germany).

### Assessment of secondary outcomes

Secondary outcome focuses on efficacy as measured by means listed below:Imaging assessment by 18-Fluorodeoxyglucose and Positron Emission Tomography (18 F-FDG PET) in FDG-avid tumors and Magnetic resonance imaging (MRI) in non-FDG avid tumors.○ 18F-FDG PET: Response evaluated by Response Evaluation Criteria In Solid Tumors (RECIST) 1.1 and European Organization for Research and Treatment of Cancer (EORTC) criteria○ MRI: Response evaluated by RECIST 1.1.
Peripheral blood serum for safety and efficacy (e.g. tumor markers)Tumor biopsy if possible for histopathological examination.

### Pharmacokinetics

Blood samples are taken before OXY111application as well as at 3 and 6 hours after application start and 30 minutes, 1, 2 and 40 hours following application. Plasma levels of OXY111A are measured by Swiss BioAnalytics AG (Birsfelden, Switzerland) under ICH Good Laboratory Practice (GLP) conditions and validated by Food and Drug Administration (FDA) and European Medicines Agency (EMA) guidance [12].

### Ethics

This study is conducted under the principles of the Declaration of Helsinki and International Conference on Harmonisation E6 Good Clinical Practice (ICH E6 GCP) guidelines. The study protocol has been approved by the independent medical ethics committee of canton Zurich (Kantonale Ethikkommission Zürich, Switzerland, KEK-ZH-Nr. 2014-0374) and the Swiss regulatory authority Swissmedic (2015DR1009). The study protocol has been registered on an international primary trial register (ClinicalTrials.gov Identifier: NCT02528526).

## Discussion

The aim of this trial is to assess the novel antihypoxic compound OXY111A in patients with non-resectable primary and secondary tumors of the liver, pancreas and biliary tract. Hepato-pancreato-biliary and gastrointestinal tumors, as known for solid tumors, develop hypoxia with consecutive modification of hypoxia dependent pathways [1]. Despite several advantages in drug development regarding tumor angiogenesis, many other hypoxic mechanisms have not been addressed so far [2]. The novel antihypoxic compound OXY111A has been tested in several cancer animal models showing beneficial effects for both survival and low side effect profiles [6–10].In this phase Ib/IIa clinical trial, application of OXY111A will be evaluated in patients with primary and secondary HPB tumors focussing on safety and tolerability, as well as efficacy.

## Abbreviations

18F-FDG PET: 18-Fluorodeoxyglucose and Positron Emission Tomography
CT: Computed Tomography
CTC: Common Toxicity Criteria
CTCAE: Common Terminology Criteria for Adverse Events
DLT: Dose Limiting Toxicity
ECOG: Eastern Cooperative Oncology Group
eCRF: electronic Case Report Form
EMA: European Medicines Agency
EORTC: European Organization for Research and Treatment of Cancer
FDA: Food and Drug Administration
HIF: Hypoxia-Inducible Factors
ICH E6 GCP: International Conference on Harmonisation E6 Good Clinical Practice
ICH GLP: International Conference on Harmonisation Good Laboratory Practice
IIT: Investigator Initiated Trial
IMP: Investigational Medical Product
ITPP: Myo-inositol trispyrophosphate
MRI: Magnetic resonance imaging
MTD: Maximum Tolerated Dose
NF-κB: nuclear factor 'kappa-light-chain-enhancer' of activated B-cells
NOAEL: No Observed Adverse Effect Level
OCT4: Octamer binding transcription factor 4
OXY111A: Study drug name of the generic myo-inositol trispyrophosphate
pO_2_: Oxygen partial pressure
RECIST: Response Evaluation Criteria In Solid Tumors
TET: Treatment- Emergent Toxicity
VEGF: Vascular Endothelial Growth Factor
